## Abstract

**Background:**

Early pre-hospital initiation of blood pressure (BP) lowering could improve outcomes for patients with acute stroke, by reducing hematoma expansion in intracerebral hemorrhage (ICH), and time to reperfusion treatment and risk of intracranial hemorrhage in ischemic stroke (IS). We present the design of the fourth INTEnsive ambulance-delivered blood pressure Reduction in hyper-ACute stroke Trial (INTERACT4).

**Methods:**

A multi-center, ambulance-delivered, prospective, randomized, open-label, blinded endpoint (PROBE) assessed trial of pre-hospital BP lowering in 3116 hypertensive patients with suspected acute stroke at 50+ sites in China. Patients are randomized through a mobile phone digital system to intensive BP lowering to a target systolic BP of < 140 mmHg within 30 min, or guideline-recommended BP management according to local protocols. After the collection of in-hospital clinical and management data and 7-day outcomes, trained blinded assessors conduct telephone or face-to-face assessments of physical function and health-related quality of life in participants at 90 days. The primary outcome is the physical function on the modified Rankin scale at 90 days, analyzed as an ordinal outcome with 7 categories. The sample size was estimated to provide 90% power (*α* = 0.05) to detect a 22% reduction in the odds of a worse functional outcome using ordinal logistic regression.

**Discussion:**

INTERACT4 is a pragmatic clinical trial to provide reliable evidence on the effectiveness and safety of ambulance-delivered hyperacute BP lowering in patients with suspected acute stroke.

**Trial registration:**

ClinicalTrials.gov NCT03790800. Registered on 2 January 2019; Chinese Trial Registry ChiCTR1900020534. Registered on 7 January 2019. All items can be found in this protocol paper.

**Supplementary Information:**

The online version contains supplementary material available at 10.1186/s13063-021-05860-y.

## Administrative information

Note: The numbers in curly brackets in this protocol refer to SPIRIT checklist item numbers. The order of the items has been modified to group similar items (see http://www.equator-network.org/reporting-guidelines/spirit-2727-statement-defining-standard-protocol-items-for-clinical-trials/).

## Introduction

### Background and rationale {6a}

Despite stroke being a major cause of loss in disability-adjusted life-years (DALYs) [1], there are few proven treatments and most are limited by short therapeutic time windows [2, 3]. Intensive blood pressure (BP) lowering is an attractive treatment, as several low-cost antihypertensive agents are widely available, and there is strong epidemiological data supporting the frequent occurrence [4] and prognostic significance of hypertension in both ischemic stroke (IS) or intracerebral hemorrhage (ICH) [5]. However, two of the largest trials of intensive BP lowering in acute ICH had inconsistent effects on functional recovery, despite the treatment being shown to be safe and able to attenuate hematoma growth [6–8]. Similarly, the Enhanced Control of Hypertension and Thrombolysis Stroke Study (ENCHANTED) showed that intensive BP lowering specifically in patients thrombolyzed for acute IS failed to improve functional recovery despite reducing the risk of intracranial hemorrhage [9]. There is also uncertainty over the optimal level of BP control in patients with IS due to large vessel occlusion treated with mechanical thrombectomy [10].

Despite these caveats, use of BP lowering in the pre-hospital setting has attracted attention in potentially being able to reduce hematoma expansion in ICH, and shorten the time to initiate reperfusion therapy and reduce subsequent risk of intracranial hemorrhage in IS. However, concerns have been raised by results of the second Rapid Intervention with Glyceryl trinitrate in Hypertensive stroke Trial (RIGHT-2). Not only was there no overall improvement in functional outcome from the use of a transdermal glyceryl trinitrate (GTN) patch in patients with presumed stroke, but there were worse outcomes in those with a final diagnosis of ICH [11]. This work has highlighted the potential for enhanced bleeding in relation to vasodilation and antiplatelet effects of GTN and possibly other BP lowering agents [12], as well as fuelling debate over the promotion of cerebral ischemia within the vulnerable penumbra of IS from such an approach [13].

Thus, we initiated the fourth in a series of early intensive BP lowering trials, the INTEnsive ambulance-delivered blood pressure Reduction in hyper-ACute stroke Trial (INTERACT4), as a pragmatic, multi-center, ambulance-delivered, prospective, randomized, open-label, blinded endpoint assessment (PROBE) study to determine the effectiveness and safety of hyperacute BP lowering for suspected acute stroke in China. Herein, we report the final version of the trial protocol, compliant with the Standard Protocol Items: Recommendations for Interventional Trials (SPIRIT) reporting guideline, with sub-title labeled by SPIRIT item number.

## Objectives {7}

### Hypothesis

Hyperacute intensive BP lowering initiated in the ambulance can improve functional outcome in patients with suspected acute stroke.

### Research questions

Compared to guideline-recommended BP management, does hyperacute intensive BP lowering initiated in the ambulance:
Improve functional outcome in patients with acute stroke?Prove to be safe in all patients with suspected acute stroke?Reduce the likelihood of death, death or dependency, and duration of hospitalization and improve physical function, health-related quality of life (HRQoL), and living circumstances?Reduce hematoma expansion specifically in patients with a final diagnosis of ICH?Increase access to reperfusion therapies (thrombolysis and/or thrombectomy) in shorter time from symptom onset and reduce the risk of intracranial hemorrhage and size of cerebral infarction, specifically in patients with IS?Show no heterogeneity in the treatment effect across certain types of patients?Provide cost benefits?

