### Outcomes {12}

The primary outcome is functional recovery on the modified Rankin scale (mRS) measured by structured interview at 3 months, with analysis as an ordinal outcome (shift across all seven scoring categories of physical function that range from 0 to 5, with death as 6) [14].

Secondary outcomes include:

• For ICH patients—hematoma volume at presentation and 24 h, with analysis as dichotomized outcomes of relative (> 33%) and absolute (> 6 mL) growth over 24 h

• For IS patients—time to, and rate of, reperfusion treatment (thrombolysis and/or thrombectomy); infarct size on MRI within 2 days after stroke onset; and frequency of symptomatic intracranial hemorrhage, measured centrally with standard definitions

• For all stroke patients—functional outcomes (death or dependency [mRS scores 3-6]) at 3 months; separately on death or dependency at 3 months; death or neurologic deficit progression measured by National Institutes of Health Stroke Scale (NIHSS) scores [15] at 24 h and 7 days, with analysis as a continuous outcome using linear regression with adjustment for baseline score; and length of hospital stay, place of residence, and health-related quality of life (HRQoL) according to the EuroQoL Group 5-Dimension self-report questionnaire (EQ-5D) [16], all at 3 months

Safety outcomes in all participants including those with a transient ischemic attack and stroke mimic will be recorded for the duration of follow-up. They will be assessed as all-cause and cause-specific SAEs and categorized according to standard organ system-specific criteria.

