## Statistics methods

### Statistical methods for primary and secondary outcomes {20a}

The intention to treat (ITT) principle will be applied in the main analysis, for all participants with presumed acute stroke as if they had received the intervention to which they were supposed to receive, irrespective of whether or not the treatment was actually received, and regardless of subsequent withdrawal from treatment or deviation from the protocol. The primary endpoint of functional recovery at 90 days will be assessed using the mRS score and analyzed using adjusted ordinal logistic regression. The intervention effect will be estimated as the common odds ratio (OR) and its 95% confidence interval (CI). The model will be adjusted by the stratification variables (region, age, and FAST score) as well as pre-morbid mRS score. In case of violation of the proportional odds assumption, the common OR and 95% CI will still be reported; however, a sensitivity analysis will be undertaken using linear regression and treating the mRS score as a continuous variable, thus estimating the effect of the intervention as an adjusted mean difference in mRS score. As a reference, an unadjusted sensitivity analysis without any baseline covariate being included will also be undertaken. The study will use a hierarchical approach for analysis of the study populations, starting with a primary analysis of all participants with a confirmed stroke (ICH or IS) and progressing to a secondary population of all randomized patients (i.e. including ICH, IS, transient ischemic attack, and mimics). A per-protocol (PP) analysis will also be undertaken only for those patients who strictly adhered to all aspects of the protocol. Multiplicity will be controlled by sequential gatekeeping. The primary population will be analyzed first with p threshold of 0.05. If the primary population shows *p* ≤ 0.05 on the primary outcome analysis, then the secondary population will next be analyzed also in a hypothesis-confirming manner with *p* threshold of 0.05. If the primary population shows *p* > 0.05, then the secondary population will next be analyzed in an exploratory manner (with nominal *p* threshold of 0.05). No further adjustment for multiplicity is planned since all secondary analyzes are hypothesis-generating and designed to support the primary analysis.

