Binary endpoints such as death and dependency and early neurological deterioration will be analyzed using adjusted binary logistic regression. Continuous outcomes, such as NIHSS score or changes in hematoma volume, will be analyzed using linear regression that includes the baseline outcome value (e.g. NIHSS score or hematoma volume) as a covariate.

A detailed analysis plan including mock tables will be finalized before the database is locked.

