## Discussion

INTERACT4 is a multi-center, ambulance-initiated, pre- and in-hospital-combined pragmatic clinical trial being conducted in China that aims to address ongoing uncertainties over the effectiveness and safety of early intensive BP lowering in patients with suspected stroke. The participation of a broad range of MEC administration systems in different medical resource settings across China will maximize the generalizability of the study results.

During the first year after the trial commenced, over 300 patients have been recruited at 30 hospitals in eastern (Shanghai) and western (Sichuan province) regions of China, demonstrating feasibility of the assessment and randomization systems, use of waiver of consent or brief consent, and implementation of the treatment in ambulance settings in both high- and low-medical resources regions. There have been several protocol deviations in the ambulance: (i) eligibility deviations, mostly from including randomized patients with an onset time beyond 2 h (mostly due to wake-up stroke) or with severe comorbid disease conditions, and (ii) intervention deviations that have included not providing BP lowering to patients allocated to the intensive group or giving BP lowering to those in control group. Short transportation times, for example averages of 15 and 20 min in Shanghai and Chengdu, respectively, are the main reason why ambulance doctors have limited time to collect baseline information or deliver treatment. However, such protocol deviations improved through 2021 after further training of investigators.

The COVID-19 pandemic caused a major challenge to the recruitment, mainly by adversely influencing the behavior of patients with suspected stroke symptoms [20]. More than half of the screen failure reasons were because of a presentation time beyond the inclusion criteria of 2 hours from symptom onset. Although COVID-19 was well controlled in China by mid-2020, these late-presenting patients (or their family members) indicated that they postponed calling the emergency hotline due to concerns of “getting infected” from being exposed at a “high-risk” hospital; their first reaction was to wait and hope that the symptom(s) would mitigate or disappear. Since the recruitment schedule was slower than planned across the two initial regional centers (Shanghai and Chengdu), the TSC decided to expand the study to other regions and hospitals in 2021.

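### Time to reperfusion: the outcome list fixes no time origin and no stated model takes out the delay before randomisation, which costs precision on a secondary outcome

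*Protocol article*

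**What the plan says.** All references are to the protocol article.

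- **Research questions (Objectives {7})** ask about "access to reperfusion therapies (thrombolysis and/or thrombectomy) in shorter time from symptom onset". This is the only place that attaches a time origin to reperfusion as an outcome.
- **Outcomes {12}** lists, for ischaemic stroke, "time to, and rate of, reperfusion treatment (thrombolysis and/or thrombectomy", with no origin.
- **Eligibility criteria {10}** limit entry to 2 h, counted from when the patient was last seen well. That is not always the same clock as symptom onset.
- **Discussion** reports breaches of that limit: "eligibility deviations, mostly from including randomized patients with an onset time beyond 2 h (mostly due to wake-up stroke". It gives no count and says deviations became fewer after further training.
- **Statistical methods {20a}** says that continuous outcomes, with NIHSS score and change in haematoma volume as examples, "will be analyzed using linear regression that includes the baseline outcome value (e.g. NIHSS score or hematoma volume) as a covariate". For the primary model it says: "The model will be adjusted by the stratification variables (region, age, and FAST score) as well as pre-morbid mRS score". Neither sentence names a delay variable.
- The same section states that "all secondary analyzes are hypothesis-generating and designed to support the primary analysis".

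**The concern.** Time from onset to reperfusion has two parts: onset to randomisation, and randomisation to treatment. The first is complete before allocation, so the intervention can act only on the second. If the whole interval is analysed and the first part is not adjusted for, differences between patients in how late they were reached enter the outcome as noise.

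The stated remedy for such noise, adjustment for the baseline value of the outcome, is not available here, because nobody has a time to reperfusion at baseline. Onset-to-randomisation time would do that job, but no section names it.

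Shorter time to reperfusion is part of the rationale in the Abstract and Background. Average transport times are given as 15 min in Shanghai and 20 min in Chengdu, so a real gain may be a matter of minutes. A gain of that size is easily blurred by up to two hours of earlier delay.

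**Working it through.** **The plan's own figures.** The article states no effect size, standard deviation or number of patients for time to reperfusion, so there is no figure to reproduce on this point. The 3116 belongs to the primary outcome. The standard proportional-odds formula (two-sided 0.05, 90% power, odds ratio 0.78, the stated mRS distribution) gives 2096 evaluable patients, and 2096/(0.70 × 0.95) ≈ 3151, within 1.1% of 3116. Nothing below bears on it.

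**Formulas.** Let s1 be the SD of onset-to-randomisation time, s2 the SD of randomisation-to-treatment time, and ρ their correlation.

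- SD counted from onset, unadjusted: √(s1² + s2² + 2ρ·s1·s2)
- SD counted from randomisation: s2
- Residual SD with onset-to-randomisation time as a covariate: s2·√(1 − ρ²)

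The ratio of the first to the second is the ratio of confidence interval widths.

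**Inputs.** All SDs and correlations are assumptions: s1 from 15 to 35 min (a uniform spread over the permitted 0 to 120 min gives 120/√12 = 34.6) and s2 from 30 to 60 min.

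**Width from onset divided by width from randomisation:**

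| s1 / s2 (min) | ρ = −0.3 | ρ = 0 | ρ = +0.3 |
|---|---|---|---|
| 15 / 60 | 0.96 | 1.03 | 1.10 |
| 25 / 45 | 0.99 | 1.14 | 1.28 |
| 30 / 60 | 0.97 | 1.12 | 1.24 |
| 34.6 / 45 | 1.06 | 1.26 | 1.43 |
| 34.6 / 30 | 1.28 | 1.53 | 1.74 |

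Example for 25/45 at ρ = 0: √(625 + 2025) = 51.5, and 51.5/45 = 1.14. Over the whole assumed grid the range is 1.03 to 1.53 at ρ = 0, 1.10 to 1.74 at +0.3, and 0.95 to 1.28 at −0.3. The onset clock is no wider once ρ ≤ −s1/(2·s2), which for 25/45 is −0.28.

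**In minutes.** With 400 reperfused patients (an illustrative number), 1:1, and SDs 25/45, the 95% half-width is 1.96 × 51.5 × √(4/400) = 10.1 min from onset and 1.96 × 45 × √(4/400) = 8.8 min from randomisation.

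**Simulation.** 4000 runs were made with 400 patients each, delay uniform on 0 to 120 min and independent of later time, post-randomisation SD 45 min, and a true effect of −10 min:

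| Analysis | Mean estimate (min) | SE (min) |
|---|---|---|
| From onset, unadjusted | −9.9 | 5.58 |
| From randomisation | −9.9 | 4.42 |
| From onset, adjusted for delay | −9.9 | 4.43 |

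The unadjusted onset clock has an SE about 26% larger (5.58/4.42), with no bias. The covariate recovers essentially all of that loss.

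**Does the remedy depend on ρ?** In large samples, no. For 25/45 at ρ = −0.3 the SDs are 44.4 (onset), 45.0 (randomisation) and 42.9 (onset with covariate). The adjusted analysis is never worse than either unadjusted clock.

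**The case against.** The case on the other side is substantial, and most of it stands.

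- **The analysis is not fixed.** A reader might infer that the trial has committed itself to an unadjusted comparison of means from symptom onset. The documents do not go that far. The origin appears in a research question, not in the outcome definition, and the sentence on continuous outcomes does not name time to reperfusion. The article also defers detail to an analysis plan to be finalised before database lock, and that plan could add the covariate.
- **Onset to reperfusion is a legitimate quantity.** It is the total time the research question asks about, and the estimate is unbiased when delay is balanced between the arms among the patients compared. That is a reason to keep the onset clock and adjust, not a reason to leave the delay in.
- **Widening is not certain.** If late presenters are treated faster once in hospital, the correlation is negative and the onset clock may be no wider. This weakens any flat statement that the interval widens. It does not weaken the covariate, which helps or is neutral for any correlation.
- **Wake-up strokes.** A reader might infer from "randomized patients with an onset time beyond 2 h (mostly due to wake-up stroke" that a few very long times would dominate the comparison. The article gives no number of such patients and no share among those reperfused, who are the only ones with a time. It also stresses limited time windows for reperfusion, so these patients may be under-represented there. No figure for their effect can be supported.

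What remains is that the one origin stated, read with the one model stated for continuous outcomes, leaves pre-randomisation delay in the outcome, and a covariate that should need no new data would take it out.

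**Conclusion.** The point holds as a minor one. The time origin should be fixed in the outcome definition, and delay before randomisation should be adjusted for. Under the assumed SDs and zero correlation, the cost of leaving it in is a confidence interval about 3 to 53% wider, roughly 10 to 25% in the middle of that range. It is larger with positive correlation and can vanish with negative correlation. These sizes rest wholly on assumed SDs, because the article gives none.

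The cost is precision only, with no bias and no effect on type I error, and it falls on one hypothesis-generating secondary outcome. The primary mRS analysis and the 3116 are unaffected. Which patients have a reperfusion time at all is a separate question and is not judged here.

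**What to change.** In Outcomes {12}, state the origin of time to reperfusion: symptom onset or last seen well, one of the two, used throughout. In Statistical methods {20a} or the analysis plan, include the time from that same origin to randomisation as a covariate in the model for this outcome. Report randomisation-to-treatment time as a supporting analysis.

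In a linear model with the delay as a covariate, the treatment estimate is identical whether the outcome is counted from onset or from randomisation. The trial's own question is therefore kept.

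The cost is a sentence or two. Time last seen well is needed for eligibility and randomisation is electronic, so no new data should be needed if last seen well is the origin. If symptom onset is chosen, the plan should say what is used when onset was not witnessed.

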## Trial design {8}

The INTERACT4 study is a multi-center, ambulance-delivered, prospective, randomized controlled, open-label, blinded outcome assessed (PROBE) trial conducted through a network of regional hospital clusters, where a total of 3116 patients with suspected acute stroke are planned to be recruited across 50+ hospitals in China. Potentially eligible patients will be recruited by either of two mechanisms: (i) waiver of consent to the intervention in the ambulance, and written consent for follow-up obtained in hospital; or (ii) consent to the intervention via a brief written consent form in the ambulance, and written consent for follow-up in hospital (if a waiver of consent is not approved by the local ethics committee). Randomized allocation of the intervention will be done in a 1:1 ratio, using a central, automated, mobile-phone accessed mini-program electronic software, with stratification based on region, age (≥ 65 vs < 65 years) and Face/Arm/Speech/Time (FAST) deficit severity score (score 3-4 vs 2). Ambulance staff are trained in the study protocol, covering approaches to assessment, randomization, treatment, and collection of key baseline data. All information in ambulance, including basic demographics, randomized treatment allocation, and BP measurement and treatment details, are collected through the mobile electronic database system which is connected to investigator clinicians at local/regional hospitals. Other relevant documents, such as the consent forms and BP charts, are handed over to hospital investigators as part of the transfer of care process. Endpoint assessments are blinded to treatment allocation. A schema of the study design is provided (Fig. 1).

**Fig. 1 Fig1:**
[figure not shown]
Study flow chart. Footnote: BP indicates blood pressure, CT computerized tomography, FAST Face/Arm/Speech/Time scale, GCS Glasgow coma scale, MRI magnetic resonance imaging, NIHSS National Institute of Health Stroke Scale, SBP systolic blood pressure

## Methods: participants, interventions, and outcomes

### Study setting {9}

The trial is being conducted at approximately 3–4 medical emergency centers (MECs) that provide ambulance services linked to hospitals in China covering an eastern area of high-level of resources (i.e., Shanghai, Jiangsu and Shandong provinces) and western and northern areas with lower levels of resources (i.e., Sichuan, Yunnan, Shanxi, and Inner Mongolia). A full list of collaborators can be found in Additional file 1. List of INTERACT4 collaborators. The study involves two different types of ambulance administration systems. The first is an independent organization whereby staff (medical and driver) are managed and dispatched from a central MEC to transfer patients to hospitals within a region. This is the situation for the district of Pudong (population 5.5 million over 1400 km^2^) in Shanghai, where the government MEC takes responsibility for the administration of all ambulance and emergency staff in the population which is served by 8 hospitals. The other model of MEC is more common in China, whereby ambulances are owned, and staff (medical and driver) employed and dispatched from individual hospitals within a region. This is the situation for the Chengdu area, where approximately 30 hospitals, each with their own ambulance service, are participating in the study.

